#### Recruitment {15}

Recruitment for the intervention study consists of selecting members to target with SMS messages from the NHIS database and the verified number sample. The phone number verification exercise which was conducted in September 2023 will ensure that a high percentage of targeted individuals can be successfully contacted and thereby enrolled. The remaining participants are recruited and enrolled automatically from the NHIS database right before the start of the intervention, which ensures that a sufficient number of individuals will be successfully contacted, despite the limitations stemming from outdated or shared phone numbers.

For the quantitative follow-up survey, we recruit the same 280 participants which had already been surveyed as part of a preliminary implementation survey in February–March 2023 and which are registered NHIA members meeting the eligibility criteria of this study. For the transferability and international scale-up research, we recruit participants in the selected target countries Kenya, Tanzania, Uganda, and Nigeria. We adopt systematic reviews of both peer-reviewed and grey literature, as well as a qualitative approach to collect data using individual semi-structured interviews (with stakeholders) as well as focus groups (with informal sector workers). The stakeholders are sampled purposively [31] from institutions involved in the development and implementation of the existing digital technologies for health financing (DTHF). We chose purposive sampling as the method as it is appropriate for identifying and selecting individuals or groups of individuals who are especially knowledgeable about or experienced in the subject matter [32]. Stakeholders who respond to our request and are available at the time of our study will be interviewed. We will use community recruitment for the informal sector workers. We will purposefully select participants and (e.g., home visits, door-to-door, friends, or family, markets) based on high percentages of informal workers in particular districts of the capital city in each of the countries. Enrolment is not limited by geographic location. The strata used for purposive sampling include the variables (stakeholders = age, gender, years working in the institution, role; informal sector workers = age, gender, insurance status, place of residence). Informal workers will be recruited by convenience sampling techniques based on their availability and willingness to take part in the study. Sampling will continue until saturation [33], meaning no new themes or codes emerge from additional interviews and focus group discussions.

### Assignment of interventions: allocation

#### Sequence generation {16a}

To select the unverified sample, we randomly draw 240,000 phone number clusters from a total of 1,128,542 eligible individuals in the NHIS database who were not already identified during the verification exercise. As phone numbers are frequently re-assigned by the phone companies or passed on to relatives and friends, all unverified individuals with a phone number on file that is shared with someone in the verified sample are excluded to prevent spillovers. We then split our verified and unverified samples into the expiration date groups 1, 2, and 3 as described above. In order to prevent spill-overs between the groups, individuals in the auxiliary groups (2, 3) who share a phone number with an individual in the main group (1) are also removed from the sampling population before randomization. Group 1 is cluster-randomized by phone number into the arms 1R (reminders), 1 A (autorenewal), and 1 C (control) with 1:1:1 proportion. Group 2 are cluster-randomized by phone number into the arms 2R (reminders), 2 A (autorenewal), and 2 C (control) with 1:1:1 proportion. Group 3 is cluster-randomized by phone number into arms 3 A (autorenewal) and 3 C (control) with 1:1 proportion. The randomizr command executed in Stata (15.1) uses a computer-generated sequence to randomly assign treatment by assigning a number between 0 and 2 (for groups 1–2) and 0 and 1 (for group 3) to each individual phone number cluster. The researchers pass on the allocation list with the anonymous unique identifiers to the technical implementation team, which executes the sending of the messages according to this allocation. Researchers do not remain blinded after the allocation has been completed in order to begin monitoring technical functioning and outcomes.

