### *Eligibility criteria* {10}

Participants must have active or recently expired NHIS membership at the starting date of the intervention. If expired, the expiration date of their insurance must be no older than 1 October 2022.Participants must be identified as residents of the Kumasi districts either through the location in their member file in the NHIS database or through the survey or phone number verification exercise conducted in 2023.Participants must have a phone number which is registered as the primary phone number for no more than 6 NHIS members residing in Kumasi.

Often, the same phone number is used by mobile money vendors or community workers to manage the NHIS insurance membership for a larger group of community members who need help with mobile renewal or who do not have access to their own phone or phone number. Receiving reminders for more than 6 individuals may become a significant nuisance for the main phone number owner. In addition, such messages may be unlikely to reach intended recipients, as they are unlikely to reside in the same household. Therefore, we exclude phone numbers shared by more than 6 individuals.

During a phone number verification exercise conducted by the NHIA in September 2023, a group of 64,646 NHIS members in Kumasi was surveyed in order to verify or update their contact details and mobile phone number. All individuals who were surveyed as part of this exercise, the “verified number sample,” are recruited as participants. The individuals surveyed during the preliminary implementation research survey in February and March 2023 were also included in this verified sample (if they were NHIS members and fit the eligibility criteria). Furthermore, any individual identified as a Kumasi resident in the database who was not included in the verification exercise and fulfills the inclusion criteria is eligible to be randomly selected into the “unverified number sample,” which forms the remainder of the participants. The verified sample consists of a group of 61,097 eligible individuals, the unverified sample consists of 281,281 eligible members which were randomly drawn from all eligible Kumasi residents in the NHIS database.

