## Interventions

### Explanation for the choice of comparators {6b}

We break down our samples into 3 groups based on their membership status and expiration dates. Group 1 contains all individuals with active insurance and an expiration date during the intervention period. Group 2 contains all individuals with a currently expired membership and expiration date between 1 October 2022 and the end of the pre-intervention period. Group 3 contains all members with active insurance and an expiration date after the planned end date of our intervention period. We do this because expired members require different reminders and autorenewal messages than active members, and because those with a renewal date during the intervention phase receive messages around their expiration dates which individuals with renewal date outside of this time frame cannot receive. Furthermore, we expect that individuals with expired insurance may react differently than individuals with active insurance, and that those with more imminent renewal dates may respond differently than those whose renewal dates are still far away. We randomly allocate treatment within each group, clustering individuals by phone number to prevent spillovers. Group 3 is only assigned autorenewal or control, because the renewal window opens 90 days before expiration, therefore sending reminders to a group whose insurance expires in 6 months at the earliest would not be sensible.

Due to the randomization, the treatments and control within each expiration date group (1, 2, 3) arms only differ by the treatment status. Individuals in the control arms will not receive SMS prompts for renewal or autorenewal, but will otherwise receive usual communications from the NHIA which are not related to this trial. Only participants assigned to be treated in the autorenewal arm will be able to sign up for the autorenewal platform as primary users, but will be able to add other individuals (typically dependents and other family members) to their renewal plan and pay for their renewals. All other individuals will be able to access the USSD Menu of the autorenewal platform through the short-code, but will not be able to sign up for the service. Instead, they will be shown an error message informing them that this platform is still undergoing testing and may be made available at a later date (Fig. 1).

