#### Strategies to improve adherence to interventions {11c}

In order to reduce technological and logistical barriers, the NHIS Helpline and local NHIA office staff will be trained to answer questions about the autorenewal system and assist with enrolment if needed.

Individuals with a phone number shared by more than 5 people are excluded from the trial in order to prevent excessive messaging to a single number, which would increase likelihood of opting out.

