## Statistical methods

### Statistical methods for primary and secondary outcomes {20a}

Descriptive statistics for each treatment arm at baseline will summarize sociodemographic characteristics as means, percentages, or counts with standard deviations. The primary outcome will be assessed as the difference in renewal rates between each treatment and its corresponding control group, comparing the difference between those who received renewal reminders (1R, 2R) or autorenewal prompts (1A, 2 A, 3 A) against the respective control group (1C, 2 C, 3 C). Specifically, we compare 1R vs. 1 C, 1 A vs. 1 C, 2R vs. 2 C, 2 A vs. 2 C, and 3 A vs. 3C. The primary outcome is rate of successful renewals in each group. The primary endpoint is the effect size, estimated with a logistic regression of treatment status on insurance outcome, and reported as an odds ratios with significance levels (*p* values and 95% confidence intervals). To assess whether reminders resulted in less or in shorter coverage gaps, we will conduct a duration analysis, comparing time-to-renewal between the treatment arms using Kaplan–Meier curves and Weibull regressions. All effect sizes will represent an intent-to-treat (ITT) effect, as we cannot be certain if a treatment reached the intended recipient. The secondary outcomes will be assessed using descriptive statistics and logistic regressions in order to compare the likelihood of signing up for autorenewal, and the likelihood of a successful renewal occurring, conditional on having signed up for autorenewal, across the different expiration date groups. The results will be reported as absolute differences and odds ratios. We cluster-randomize individuals by phone number in order to avoid having individuals with the same phone number in different treatment arms, which could result in spill-overs. For the analysis, we use individual-level analysis for two reasons: (1) because the treatment is addressed to each individual and timed according to individuals’ expiration dates, making this an individual-level treatment, and (2) ~ 85% of phone number clusters contain only one individual, making an application of a mixed-effects model difficult, as there would be nearly as many random intercepts as there are observations. However, we do use clustered standard errors in the analysis to account for possible intra-cluster correlations.

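### As written, a phone number shared by a Group 2 and a Group 3 member can be allocated to two arms; separately, the sharing cut-off is given as both 6 and 5

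*Protocol article*

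**What the plan says.** All references are to the protocol article.

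- **Purpose of clustering.** Section {20a}: "We cluster-randomize individuals by phone number in order to avoid having individuals with the same phone number in different treatment arms".
- **Level of randomisation.** Section {6b}: "We randomly allocate treatment within each group, clustering individuals by phone number to prevent spillovers". Section {16a} gives the ratios: "Group 2 are cluster-randomized by phone number into the arms 2R (reminders), 2 A (autorenewal), and 2 C (control) with 1:1:1 proportion", and Group 3 into 3A and 3C at 1:1. The allocation numbers differ by group (0 to 2 for Groups 1 and 2, 0 to 1 for Group 3).
- **Exclusions across samples and groups.** Section {16a} has two. Between samples: "all unverified individuals with a phone number on file that is shared with someone in the verified sample are excluded to prevent spillovers". Between groups: "individuals in the auxiliary groups (2, 3) who share a phone number with an individual in the main group (1) are also removed".
- **Sharing cut-off.** Section {10}: "Participants must have a phone number which is registered as the primary phone number for no more than 6 NHIS members". Section {11c}: "Individuals with a phone number shared by more than 5 people are excluded from the trial".

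**The concern.** Randomising by phone number within a group protects only numbers that lie wholly inside that group. The plan recognises this, because it adds a removal rule for numbers that reach across groups. That rule covers Group 1 with Group 2 and Group 1 with Group 3, but says nothing about Group 2 with Group 3. Section {16a} splits the samples into groups after the phone-number clusters are drawn, so one cluster can hold an expired member (Group 2) and an active member whose cover ends after the intervention (Group 3). Such households are plausible: the autorenewal menu is built so that a user can add a spouse or child.

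Three of the five comparisons listed in {20a} could be touched: 2R v 2C, 2A v 2C and 3A v 3C. A control member's phone could receive trial prompts meant for the other member. Section {14} itself says that spill-overs could attenuate the effect.

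The cut-off conflict is a separate matter. A number with exactly six members is eligible under {10} and excluded under {11c}.

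**Working it through.** **1. The plan's own count.** Section {14} gives 30,000 clusters per unverified arm, and {16a} gives 240,000 clusters drawn. There are eight arms (1R, 1A, 1C, 2R, 2A, 2C, 3A, 3C), and 8 x 30,000 = 240,000, an exact match.

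**2. Allocation of a number that spans Groups 2 and 3.** Inputs from {16a}: 1/3 for each of 2R, 2A, 2C and 1/2 for each of 3A, 3C. The draws are taken as independent because each group is randomised on its own. Each pair then has probability 1/3 x 1/2 = 1/6.

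| Pair | Treatment types | A control member beside a treated one? |
|---|---|---|
| 2R, 3A | differ | no, both treated |
| 2A, 3A | same | no |
| 2C, 3A | differ | yes |
| 2R, 3C | differ | yes |
| 2A, 3C | differ | yes |
| 2C, 3C | same | no |

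- Different treatment types: 4/6 = 67%.
- One member control and the other treated: 3/6 = 50%. This is the figure relevant to contamination.
- Given 2C, the other member is in 3A with probability 1/2.
- Given 3C, the other member is in 2A with probability 1/3, or in 2A or 2R with probability 2/3.

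**3. Share of the control arms affected.** The article does not give the share *s* of a group's numbers that span Groups 2 and 3, so *s* is an assumption. Section {20a} puts single-member clusters at about 85%, which leaves about 15% shared in any way. I use 15% as an illustrative upper end, not a strict bound. Affected share = *s* x the conditional probability above.

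| Assumed *s* | 2C beside 3A (x 1/2) | 3C beside 2A (x 1/3) | 3C beside 2A or 2R (x 2/3) |
|---|---|---|---|
| 1% | 0.5% | 0.3% | 0.7% |
| 5% | 2.5% | 1.7% | 3.3% |
| 15% | 7.5% | 5.0% | 10.0% |

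**4. Direction.** Because the draws are independent, the chance that a Group 2 member's phone also carries a 3A member is 1/2 in 2R, 2A and 2C alike. The exposure is balanced between arms, so it does not confound. It dilutes where the stray prompt resembles the treatment under test, most clearly in 2A v 2C and 3A v 3C. If every affected control gained the full treatment effect, the difference in 2A v 2C would shrink by the share in the table: 2.5% of its size at *s* = 5%.

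**5. Clusters of exactly six.** The unverified sample has 281,281 members in 240,000 clusters: 281,281 / 240,000 = 1.172 per cluster. Let 85% be single, a fraction *f* have six members and the rest have two. The mean is then 0.85 + 2(0.15 - *f*) + 6*f* = 1.15 + 4*f*. Setting this to at most 1.172 gives *f* of at most about 0.5%. The 85% is rounded and may describe both samples together, so this is a rough bound.

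**The case against.** The strongest reply is that silence is not evidence. A reader might infer that numbers shared between Groups 2 and 3 were in fact left in, but the article only fails to mention them. The figure on sample composition and randomisation is not visible here, and 8 x 30,000 = 240,000 fits each number being in one arm only. This stands as a limit on the point: it concerns the rule as written. It does not settle the matter, because both figures are round targets, no one-arm rule is stated, and the count does not cover the verified sample.

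A reader might also take the 67% discordance as the contamination rate. That is too strong. It includes 2R with 3A, where no control is exposed. Likewise, the 2/3 for 3C counts a reminder that is addressed to another named person and gives that person's expiry date. Section {6b} says that reminders would make no sense for Group 3. Being on a phone that receives a prompt is also not the same as being treated: anyone outside the autorenewal arms gets an error message on trying to sign up.

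The route by which an autorenewal user adds someone from another arm is already anticipated. Section {20c} monitors such registrations and allows an instrumental-variable analysis. That answers this route in part, since the analysis is optional. It does not name prompts that arrive on a control member's shared number.

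Finally, {11c} may be a slip for more than five other people, which would agree with {10}. As worded, the two sections still conflict.

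**Conclusion.** The point holds for the text. The removal rule in {16a} leaves out numbers shared by Groups 2 and 3, so the property that {20a} gives as the reason for clustering is not guaranteed. For a spanning number, the chance of a control and a treated member on one phone is 50%, assuming independent draws.

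The effect on results is probably slight dilution of 2R v 2C, 2A v 2C and 3A v 3C. It depends on the unreported share of spanning numbers. The 85% figure suggests that this share is small, although the article does not say whether clusters were counted before or after the split into groups. In the verified sample Group 3 is very small, so the share there could differ.

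A reader might extend the concern to the main comparisons, 1R v 1C and 1A v 1C. The documents do not support that, because the stated rule protects Group 1 from this route.

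The 6 v 5 conflict is a genuine contradiction about who is eligible. On the rough bound above it concerns at most about 0.5% of unverified clusters, so it does not make the analysis population materially uncertain.

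**What to change.** 1. From the baseline allocation list, flag every phone number present in both Group 2 and Group 3, in the verified and unverified samples. Report the count for each of the six arm pairs.
2. Keep the all-randomised intention-to-treat analysis as primary. Add a sensitivity analysis of 2R v 2C, 2A v 2C and 3A v 3C that excludes flagged numbers. The flag rests only on pre-randomisation data, so the exclusion keeps the randomised comparison intact. The interventions are complete and the researchers are not blinded after allocation, so this exclusion should not become a new primary population.
3. If the code already removed these numbers, or gave each number a single arm, state that in {16a}. Steps 1 and 2 then fall away.
4. Reconcile the cut-offs in {10} and {11c} with the code that was run, and report the number of clusters with exactly six members.

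The cost is one flag on an existing list, three repeated regressions on slightly fewer members, and a few sentences of text.

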#### Concealment mechanism {16b}

The randomizr command conceals the sequence.

#### Implementation {16c}

The command randomizr is used by one of the researchers to employ the allocation sequence in each group of participants. Once selected, a participant is automatically enrolled.

## Assignment of interventions: blinding

### Who will be blinded {17a}

The control group will not be aware that they are part of the control group.

### Procedure for unblinding if needed {17b}

No procedure planned.

## Data collection and management

### *Plans for assessment and collection of outcomes* {18a}

Anonymized routine data of all trial participants is extracted from the NHIS database, and shared with the researchers. This contains the renewal transaction data of NHIS members (date of transaction, beginning and end of insurance period, fees paid, platform used for transaction), intervention status (trial arm, autorenewal registration status, opt-out status), and user information (unique identifying number, age, gender, marital status, payment category) for each participant. This data is used to assess rates of insurance renewal and of autorenewal enrolment across treatment arms and demographic subgroups.

In addition, a randomly selected sample of 280 households in Kumasi will be surveyed as part of the quantitative and qualitative follow-up survey assessing user experience, acceptability, and usability of the reminder and autorenewal service. These households are part of the verified sample and were previously surveyed in 2023 as part of a preliminary implementation and feasibility study, and will be surveyed again after the intervention is completed. The data will be collected by trained research assistants through face-to-face interviews. The quantitative follow-up survey will collect sociodemographic characteristics of households and individuals, health insurance coverage status, satisfaction with the reminders, and autorenewal option.

For the qualitative scale-up interviews, data will be collected using a semi-structured approach based on interview guides. The interview guide used for data collection will be prepared based on existing literature and the research objectives of the study.

### Plans to promote participant retention and complete follow-up {18b}

Participants can only deviate from the treatment protocol by opting out of receiving SMS messages. However, they can still be observed in the routine data after opting out, so will automatically be followed up on.

### Data management {19}

Routine data is captured automatically in the NHIS data management system. All data is anonymized being sent to researchers via a secure, password-protected cloud server, and under a non-disclosure agreement.

Data for the quantitative follow-up survey data is captured using REDCap, a secure, web-based electronic data capture system. It will be managed at the KNUST and hosted by their server. Only staff listed in the delegation log is given the unique individual password to access the internet-based data management system. The data is exported from the REDCap software into excel to validate the data and check for missing data. Submitted surveys is validated daily to ensure mistakes are seen early enough for corrections to be made and to ensure the number of interviews done tally with the data submitted to prevent data loss and ensure data uniformity. Researchers keep anonymized routine and survey data only on password-protected computers which comply with the university’s security standards. Both routine and survey data undergo plausibility checks for range and distribution of values before analysis.

Data for the qualitative scale-up interviews is collected anonymously and treated confidentially. Audio-recorded interviews will be transcribed verbatim. The data is stored on secure server at the KNUST and transferred to consortium partners in accordance with established data transfer agreement, and is only published in aggregated form in publications by the study team. The data is used for research projects and possible scientific publications of the participating project team. Participants contact details (name, e-mail address, address) are collected and stored in encrypted form, i.e., neither name, initials nor address, etc. appear in the encryption code. The data is only used to contact them for project coordination purposes and will be deleted at the end of 2024. The audio recordings are converted into text (transcribed) and then deleted. The transcription is carried out by the KNUST partner university and the text is anonymized. This means that information that allows conclusions to be drawn about participants is blacked out or changed accordingly.

